### Postoperative Care

In both groups, early active motion of the operated limb will be permitted as soon as motor function recovers from anesthesia. All participants will be instructed to begin immediate knee flexion and extension exercises, ankle and foot movements, and active calf pump exercises. No orthotic devices or physical positional measures will be utilized to restrict hip motion. However, all patients will be advised to avoid flexion, adduction, and internal rotation of the operated hip, or sitting in low chairs for at least 3 months. Walking with 2 crutches with weight-bearing as tolerated will be stimulated on the first postoperative day until the follow-up visit at 21 days, and patients will be discharged for ambulatory care as soon as ambulation is possible with comfort. Sports and activities on extreme hip motions will be discouraged for at least 3 months.

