### Secondary Outcomes

Secondary outcomes will include comparisons of QoL, joint mobility, function, satisfaction, and pain before and after the surgery, as well as radiographic parameters extracted from the immediate postoperative radiograph. The annual frequency of revision surgeries will be recorded.

QoL will be evaluated using 12-Item Short Form Health Survey version 2 questionnaire [21]. QoL is defined as an individual’s perception of their position in life in the context of the culture and value systems in which they live and about their goals, expectations, standards, and concerns [21]. The 12-Item Short Form Health Survey is an instrument for measuring QoL composed of 12 items that assess eight different dimensions of influence on QoL, considering the individual’s perception of aspects of their health in the last 4 weeks [21]. Each dimension’s score is summed up, and the final score can be between 0 and 100; the higher the score, the better the QoL [22].

Participant satisfaction assessment will be measured using a 10-point numerical rating scale ranging from 1 (very dissatisfied) to 10 (completely satisfied) [23].

Other aspects of health, such as pain, will be evaluated through the Visual Analog Scale. The Visual Analog Scale provides a simple and efficient measure of pain intensity and is used when a fast pain index that can be assigned to a numerical value is needed [24].

Radiographic parameters will include the ability to restore anatomical normality parameters on postoperative radiographs according to the surgical plan (namely the limb length discrepancy, the horizontal off-set of the hip, difference between the back of the prosthesis and the tip of the trochanter, inclination of the acetabular component, and the difference between offset obtained to the normal side) all of this using the Peekmed surgical planning software.

The annual frequency of revision surgery will be observed starting from 1 year after surgery and annually until 5 years, and up to 10 years.

All questionnaires will be administered by examiners blinded to the surgical procedure. Questionnaires will be completed using digital devices (computer or tablet).

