### Statistical Analysis

Results will be presented descriptively, with continuous data expressed as means (SD) and medians, and categorical data will be presented as means or percentages. For inferential analysis, the normality of the variables will be assessed using the Kolmogorov-Smirnov test. Dichotomous variables will be analyzed using the Fisher exact test and chi-square test, and continuous variables will be analyzed using the *t* test. Demographic data will be analyzed using ANOVA test, and the chi-square test will be used for the categorical data. In cases of non-normal distribution, appropriate nonparametric tests will be used according to the nature of the variable.

Primary outcomes, complications, and reoperations will be analyzed at 48 weeks. Paired and subgroup analyses are foreseen between periods of 3, 6, 24, and 48 weeks for the described outcomes. Results will be reported with 95% CI.

All statistical tests will be 2-sided, with a significance level of *P*=.05. Data will be analyzed using the Online Statistics Calculator, DATAtab/Numiqo (2025) [26]. Data from participants who receive additional treatments (eg, revision surgery for fractures) during study participation will be retained for intention-to-treat analysis.

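### The SF-12 asks about the last 4 weeks but appears to be compared at week 3, where a quarter of that window precedes surgery, and its eight dimensions read as one summed total

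*Protocol article*

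**What the plan says.** Under Secondary Outcomes the protocol article names the instrument: "QoL will be evaluated using 12-Item Short Form Health Survey version 2 questionnaire". It describes it as "composed of 12 items that assess eight different dimensions of influence on QoL", answered from the person's "perception of aspects of their health in the last 4 weeks". On scoring, it says that each dimension's "score is summed up, and the final score can be between 0 and 100; the higher the score, the better the QoL".

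On use, the same section promises a before-and-after comparison: "Secondary outcomes will include comparisons of QoL, joint mobility, function, satisfaction, and pain before and after the surgery". Recruitment and Preoperative Assessment confirms that a quality-of-life questionnaire is given before surgery.

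On timing, Statistical Analysis first says "Primary outcomes, complications, and reoperations will be analyzed at 48 weeks" and then "Paired and subgroup analyses are foreseen between periods of 3, 6, 24, and 48 weeks for the described outcomes". Postoperative Care has patients walking with crutches "until the follow-up visit at 21 days", so a visit at week 3 exists.

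**The concern.** Two stated rules sit badly with the intended use of the SF-12.

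**Recall.** A question about the last 4 weeks, put 3 weeks after an operation, covers some time before it. The week-3 answer then partly describes the arthritic hip. Early change is understated, and so is any early difference between the stems. Early differences are of interest here, because the Introduction cites more early pain and slower recovery with uncemented femoral fixation.

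**Scoring.** Adding eight different dimensions into one final score gives every dimension a say in the result. If the type of stem affects only some of them, the rest add noise without signal. The sentence is also hard to apply as written. If each dimension runs from 0 to 100 (an assumption), eight of them sum to 0 to 800, so a 0 to 100 total needs a rescaling that is not described. If 0 to 100 is meant per dimension, there is no single final score.

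Quality of life is part of the stated objective, so the measure should be sound even though it is a secondary outcome.

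**Working it through.** **The plan's own figure.** The article states no calculation for the SF-12. Its sample size rests on the Harris Hip Score (SD 10.5, difference 5.39, two-sided 0.05, power 80%):

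n per group = 2 × (1.96 + 0.8416)² × 10.5² / 5.39² = 59.6, rounded up to 60.

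This matches the stated 60 per group (the exact t-test gives 60.5). The SF-12 does not enter it, so nothing below changes the sample size.

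**Recall window.** Inputs: recall of 4 weeks = 28 days (Secondary Outcomes); time points of 3, 6, 24 and 48 weeks (Statistical Analysis); a visit at day 21 (Postoperative Care). Assumption: weeks are counted from surgery. For a visit on day D, the days of recall before surgery are max(0, 28 − D).

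| Visit | Day | Window (days from surgery) | Days before surgery | Share |
|---|---|---|---|---|
| Week 3 | 21 | −7 to 21 | 7 | 7/28 = 25% |
| Week 6 | 42 | 14 to 42 | 0 | 0% |
| Week 24 | 168 | 140 to 168 | 0 | 0% |
| Week 48 | 336 | 308 to 336 | 0 | 0% |

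**What 25% can do to the mean score.** Illustration only: let the week-3 answer be w × (state before surgery, B) + (1 − w) × (state after surgery, P).
- Change from baseline: wB + (1 − w)P − B = (1 − w)(P − B).
- Contrast between groups: the arms are alike before surgery in expectation, so the expected contrast is (1 − w) times the true one.
- Change from week 3 to a later visit with state L: L − wB − (1 − w)P = (L − P) + w(P − B), so it absorbs what week 3 lost.

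If all 28 days count equally, w = 0.25 and a quarter of the week-3 change and contrast is lost. If patients answer only from the days since surgery, w = 0 and nothing is lost. The document gives no basis for choosing within 0 to 25%.

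**Dilution by one total.** Assumptions, none from the document: eight dimensions of equal variance with common correlation r, an effect d on four of them, and an effect kd on the other four.
- Standardised effect on the sum of eight: 4(1 + k)d / √(8 + 56r).
- Standardised effect on the affected four: 4d / √(4 + 12r).
- Patients needed with the sum relative to the four: (8 + 56r) / [(4 + 12r)(1 + k)²].

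| r | k = 0 | k = 0.5 | k = 1 |
|---|---|---|---|
| 0.3 | 24.8/7.6 = 3.3 | 3.26/2.25 = 1.5 | 3.26/4 = 0.8 |
| 0.5 | 36/10 = 3.6 | 3.6/2.25 = 1.6 | 3.6/4 = 0.9 |
| 0.7 | 47.2/12.4 = 3.8 | 3.81/2.25 = 1.7 | 3.81/4 = 0.95 |

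The correlation matters little. The answer turns on k, on which the document is silent: a large loss if the other four dimensions do not move, a moderate one if they move half as much, and none if all eight move together.

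**The case against.** **Week-3 use is not stated.** No sentence in the text says that the SF-12 is given or analysed at week 3. The sentence just before the list of weeks names only primary outcomes, complications and reoperations, and the flowchart with the schedule is not shown. This stands as a condition on the point. It does not remove it: paired analyses across visits suit repeated scores rather than one-off events, a before-and-after comparison of quality of life is promised, and the text gives no other postoperative times for it.

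**The overlap is modest and balanced.** This also stands. At day 21, 21 of 28 days (75%) are postoperative. A reader might infer that the week-3 score is no postoperative measure at all, or that the overlap favours one stem; the figures do not support either. The overlap falls on both randomised arms alike and pulls towards no difference.

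**The scoring sentence may only be loosely worded.** It could mean that items are summed within each dimension and each dimension is put on a 0 to 100 scale. That reading is possible, though a single final score after summing dimensions points to a total. Either way the sentence needs correcting. Detail of the scoring algorithm can fairly be left to a fuller document, but a stated rule that such a document would have to override cannot.

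**The physical and mental split is not in the document.** A reader might infer that the total mixes mental with physical health and so costs three to four times the patients. The article never labels the dimensions in that way, and the multiple rests on exactly zero effect in half of them. That size is not claimed here.

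**Conclusion.** The point holds in a limited form. If the SF-12 is taken at day 21 and quality of life is among the outcomes compared at week 3, which is the most natural reading, 25% of its recall window precedes surgery. The week-3 change from baseline and the week-3 contrast between groups are then attenuated, by up to a quarter if all recall days count equally. Weeks 6, 24 and 48 are clean.

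The scoring sentence most naturally describes one total over eight different dimensions, which can dilute an effect confined to some of them. No size can be put on this from the document.

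The harm is loss of sensitivity in a secondary outcome, not bias between arms. It does not touch the Harris Hip Score, complications or the 60 per group. Nor does the document support requiring one particular summary score at 48 weeks as the quality-of-life outcome; that would be a new design choice.

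**What to change.** 1. In Statistical Analysis, state that inferential postoperative SF-12 comparisons begin at week 6, and that any SF-12 collected at week 3 is reported descriptively only. Cost: the week-3 quality-of-life comparison is lost. Pain at that visit is measured separately on the Visual Analog Scale.

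2. In Secondary Outcomes, replace the scoring sentence so that the SF-12 version 2 is analysed by its separate published scores rather than one summed total, and name the score or scores to be compared between groups. Cost: one sentence and rescoring of items already collected.

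If the schedule shows no SF-12 at week 3, the first change reduces to one clarifying sentence.

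The Results section says that the November 2025 analysis reported population characteristics, radiographic and intraoperative findings and early complications. Quality of life is not in that list, so on that account both changes can still be made before a quality-of-life comparison is reported. They should be dated and communicated as a protocol modification.

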**Methods:**

This study is a single-center, single-surgeon, single-approach, pragmatic, double-blinded, and prospective randomized trial. A total of 120 patients will be enrolled and randomly allocated in a 1:1 ratio to 2 groups: the hybrid group and the uncemented group. The incidence of complications (during and after surgery) and the restoration of normal anatomical parameters on postoperative radiographs will be assessed using radiographic parameters. Participants’ QoL, joint mobility, function, and satisfaction will be evaluated using the 12-Item Short Form Health Survey version 2 questionnaire, hip range of motion, the Harris Hip Score, and a numeric rating scale. Prosthesis survival will be analyzed using the annual revision surgery rate from 1 to 5 years, and up to 10 years.

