While most RCTs in this area of research have traditionally focused on implant survival and revision rates [4], patient-centered outcomes, QoL, and early complications have become a current hot topic. Hybrid THA yields similar short- to mid-term patient-reported outcome measures (Harris Hip Score [HHS], WOMAC, EQ-5D) compared with cemented and uncemented constructs. A 2025 systematic review of 357,748 THAs found no difference in patient-reported outcome measures between hybrid and cemented THA and no clear advantage of uncemented constructs [11]. However, the incidence of periprosthetic fracture was reported to be significantly higher with uncemented stems, especially in older adults. Moreover, a slightly higher incidence of dislocations was also reported for uncemented stems [12]. Regarding pain, direct elective THA comparisons are limited, but evidence consistently shows more early pain and slower recovery with uncemented femoral fixation due to press-fit stem insertion forces. A meta-analysis of RCTs in THA showed better short-term pain scores with cemented fixation [13]. Additionally, a large National Health Service cost-effectiveness analysis (n≈300,000) found higher postoperative EQ-5D scores with hybrid THA (0.81 vs 0.80 for uncemented), and for most patient groups, hybrid prostheses were found to be the most cost-effective [14].

Few publications on THA performance using Brazilian-manufactured materials have reported results comparable to those from other countries; however, the level of evidence and sample sizes of these studies are limited [15-17]. Additionally, early failures of previous national models, commonly used in Brazil until the 1990s, became the reason for persistent questioning about the safety and durability of Brazilian-made implants [18]. To date, no level 1 study evaluating the performance of such implants in Brazil has been identified.

This study aims to compare the clinical outcomes (function, pain, complications, QoL, and need for revisions) and radiographic outcomes of patients treated with a national hybrid prosthesis (with femoral cementation and uncemented acetabular cup) versus those receiving national uncemented prostheses of the same brand.

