### Primary Outcomes

The primary outcomes of this study will be patient-reported function and complications.

Clinical evaluation will comprise the measurement of hip ROM to assess joint mobility, and the HHS questionnaire will be applied to assess function. Hip ROM will be measured using the goniometer, with the patient lying supine, to determine joint mobility. Hip function will be assessed using the HHS, which is a THA-specific questionnaire composed of patient-reported function and physician-assessed joint ROM, including pain, function, deformity, and mobility assessment [19,20]. The HHS is scored up to 100 points, where each section has a different score, and after applying the questionnaire, all scores are summed up. Scores below 70 are considered low, scores between 70 and 80 are considered fair, scores between 80 and 90 are considered good, and scores between 90 and 100 are considered excellent [19].

The incidence of complications (during and after surgery) will be extracted from an intraoperative questionnaire completed by the surgeon, an immediate postoperative questionnaire reported by the patient, and a special severe adverse effect questionnaire, which will be filled whenever the patient requires readmission or additional surgery.

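### Prosthesis survival is set as a yearly revision rate whose time origin is unclear and which does not handle unequal follow-up

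*Protocol article*

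**What the plan says.** The Abstract (Methods) names the measure: "Prosthesis survival will be analyzed using the annual revision surgery rate from 1 to 5 years, and up to 10 years". Secondary Outcomes repeats it with a start: "The annual frequency of revision surgery will be observed starting from 1 year after surgery and annually until 5 years", and then extends it to 10 years. The same section also has a general sentence with no start time: "The annual frequency of revision surgeries will be recorded".

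Early events are handled in two other places. Primary Outcomes draws complications partly from "a special severe adverse effect questionnaire, which will be filled whenever the patient requires readmission or additional surgery". Statistical Analysis sets a separate time point: "Primary outcomes, complications, and reoperations will be analyzed at 48 weeks". It also keeps patients who have had revision surgery in the intention-to-treat analysis.

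The methods named in Statistical Analysis are Fisher, chi-square and t tests, ANOVA for demographic data, and nonparametric tests where data are not normal. No time-to-event method is named. Withdrawal From the Study treats data after withdrawal as missing, with imputation to be considered.

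**The concern.** The survival outcome has no stated time origin. If observation really begins at 1 year, the comparison starts with hips that have already lasted a year. The arms are then compared in groups selected after randomization, and a difference in early failure is lost from the outcome labelled survival. Early failure is where the Introduction points to a contrast in the literature: "the incidence of periprosthetic fracture was reported to be significantly higher with uncemented stems, especially in older adults". That sentence reports published findings and is not a prediction for this trial, but it shows why the first year matters to this comparison.

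The second part is the measure itself. A yearly frequency compared with tests for proportions needs a rule for patients who have not completed the year, have died or have left. Entry is staggered, patients may be 80 at entry, and follow-up is meant to run 5 to 10 years, so such patients are to be expected. Two analysts following the article could publish different survival figures from the same data.

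**Working it through.** **1. The plan's own figure.** The only calculated design figure is the sample size for the Harris Hip Score (Sample Size: difference 5.39, SD 10.5, power 80%, two-sided 0.05). n per group = 2 × (1.960 + 0.842)² × (10.5/5.39)² = 2 × 7.849 × 3.795 = 59.6, so 60. It reproduces. Nothing below depends on it, and no sample size is stated for revision.

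**2. The two readings of the start.**

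| | Counted from surgery, first report at 1 year | Observation begins at 1 year |
|---|---|---|
| First-year revisions count against survival | yes | no |
| Where they appear | survival outcome; also the 48-week analysis if by then | 48-week reoperation analysis only |
| Days in neither analysis | none | 337 to 364 |

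The 48-week window closes on day 48 × 7 = 336. Under the second reading the survival series opens on day 365, which leaves 28 days (28/365 = 7.7% of the year).

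**3. How many events depend on the reading.** The documents give no revision rate, so a first-year risk of 0.5% to 5% is assumed.
- Revisions among 120: 120 × 0.005 = 0.6, up to 120 × 0.05 = 6.0.
- In the 28 days, if spread evenly over the year: 0.6 × 28/365 = 0.05, up to 6.0 × 28/365 = 0.46.
- Chance of at least one in the 28 days: 1 − (1 − p × 28/365)^120 = 4% to 37%. It would be lower if risk is concentrated early.

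**4. Illustration with assumed counts.** Take first-year revisions of 1/60 and 3/60, and one later revision in each arm.
- From surgery: 2/60 = 3.3% and 4/60 = 6.7% revised, a difference of 3.3 percentage points.
- From 1 year: 1/59 = 1.7% and 1/57 = 1.8%, a difference of about 0.1 point.
- Fisher's exact test on 2/60 against 4/60 gives p = 0.68. The change is in the estimate, not in a conclusion about significance.

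**5. Follow-up available by December 2029.** Inputs: start in October 2024, and 72 operated on as of April 2025 (Results); collection expected to end in December 2029 (Abstract, Results); 120 in total (Study Design and Setting).
- Not yet operated on: 120 − 72 = 48, and 48/120 = 40%.
- Their longest possible follow-up, taking the count as at 1 April 2025, runs to 31 December 2029: 4 years 9 months. None of the 48 can complete 5 years by then.
- 48 is a minimum. Anyone operated on after December 2024 also falls short. If surgery kept to the planned 12 patients a month (an assumption), 3 × 12 = 36 were operated on by then, and 120 − 36 = 84 (70%) fall short.
- The longest follow-up possible is from 1 October 2024: 5 years 3 months. Nobody reaches 10 years by December 2029.
- Results describes an analysis of the complete population in November 2025. If all 120 had been operated on by then, the shortest potential follow-up is about 4 years 1 month, so staggered entry affects year 5 and not years 1 to 4.

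**The case against.** The ordinary reading of the Secondary Outcomes sentence is a list of reporting points, and a yearly figure first given at 1 year would naturally cover surgery to 1 year. No sentence excludes first-year revisions. This stands: a reader might infer that the plan drops them from survival, but the text only permits that reading.

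Early failures are not lost to the trial. Complications are a primary outcome, reoperations are analysed at 48 weeks, and the severe-event form has no stated cut-off. This stands too. It answers any suggestion that early failures would be hidden, but not the question of what the survival figure contains.

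A reader might also infer that the 28-day gap loses events, or that the wording could reverse the comparison between arms. Neither is supported. The gap exists under one reading only, is a gap in analysis windows and not in data capture, and holds less than half an event at the top of the assumed range. The illustration shows a difference shrinking, not reversing.

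On the estimator, a condensed article may leave survival methods to the analysis plan, and no denominator is defined here. One therefore cannot say that the plan wrongly keeps the dead or departed among those at risk. Staggered entry is also balanced by blocked 1:1 allocation, so it mainly affects the level of the year-5 figure and less the contrast, and follow-up may continue past December 2029 for the 10-year aim. What remains is that the article does not stay silent: it names a yearly rate as the measure of survival, and none of the tests it lists handles incomplete follow-up.

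**Conclusion.** The point holds as a needed clarification with a better method, at low to moderate weight on a secondary outcome. The survival outcome does not fix its time origin, and its wording can be read as leaving first-year revisions to the 48-week analysis alone. Under that reading 0.6 to 6 revisions among 120 would be outside the survival figure, on an assumed first-year risk of 0.5% to 5%.

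Separately, a yearly frequency does not handle unequal follow-up. At least 40% of patients cannot complete 5 years by the stated end of data collection; that figure follows from the documents' own dates and is relevant unless follow-up continues beyond December 2029. Deaths and withdrawals add to this, but the documents give no rates for them, so their size cannot be stated.

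**What to change.** In the Abstract and Secondary Outcomes, replace the wording that starts observation at 1 year with: counted from the day of surgery, reported at 1 year and yearly thereafter. Then:

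- Analyse time from surgery to first revision as cumulative incidence, with censoring at last contact and death as a competing event.
- State how this outcome relates to the 48-week reoperation analysis, so that each revision has a clear place in both.
- Confirm that the severe-event form records the date of revision. The article describes when the form is filled in but not its fields.

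The cost is a change of wording and a little extra analysis work, which may need software other than the online calculator named in Statistical Analysis. If the form records the date, no new data are needed. Sample size and trial conduct do not change, and most results beyond 1 year are still to come.
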